### Secondary outcomes

The secondary outcomes measured in this study include: cognitive schemas (measured using the YSQ); self-objectification (measured using the SATAQ-Internalisation); general quality of life (WHO-5 and CORE-10); self-compassion (SCS-SF); schema mode presentations (measured using the SMI); and Personality Disorder features (measured using the MCMI-III and the BSL-23).

### Intervention

The schema therapy eating disorder group (STE-g; [44]) was based on the schema mode model, with some components drawing on the schema-therapy treatment program: “Schema Focused Therapy in a Group Setting” [48]. The program consists of twenty-five 90-min sessions. All participants are provided with a patient-version workbook which corresponds with the treatment manual. The first part of the group focuses on schema psychoeducation and schema-focused cognitive behavioral strategies which help participants to identify and start challenging their schemas, whilst working on behavioral change both within and outside the group. This model assists participants to develop an individualised formulation of their own difficulties using a schema therapy framework. The highest schemas and modes are identified for each patient on the basis of their scores on relevant measures. Each session is recorded and group members are strongly encouraged to come in to watch the video should they miss a session. This is to ensure that participants do not miss any educational material, and retain a sense of connectedness with the group.

Particular emphasis is placed on linking eating behaviors to the schema modes, so that participants are able to learn about the origins and coping functions associated with their own pattern of symptoms. Avoidant coping in the group is addressed frequently by labeling the “Detached Protector” mode when it is identified either by group leaders or by other participants (i.e., both in the context of the group and when talking about eating behavior which took place between sessions). Use of over-compensatory behaviors to avoid emotions is also identified and group members are encouraged to point this out to each other empathically as the group progresses. Due to the lack of emotional awareness and emotional tolerance within the group, participants are encouraged to learn to express empathy and to ask for their emotional needs to be met within the context of the group, rather than detaching from emotional needs through eating behaviors. Schema-focused mindfulness meditation [27], is incorporated to increase awareness of urges to carry out eating disordered behaviors, modes and associated triggers and to facilitate emotional regulation.

Participants are helped to identify the origins of their negative body-image, and to link these to the development of particular modes. Body-image restructuring work involves participants learning to recognise the way in which their perception and visceral sense of their bodies differs from the perspective of their most prominent modes, and developing a compassionate “Healthy Adult” mode which is accepting and nurturing toward the body. Mode dialogues are used to enable group members to repeatedly coach each other to send the “Critical” mode away when it expresses negative assertions about the body or self (e.g. “You are ugly, fat, and nobody really likes you”). This gives group participants the opportunity to practice being in Healthy Adult mode firstly for others and then for themselves. Flashcards are used to reinforce what is learned in sessions and to help participants to challenge modes and resist eating disordered behavior between sessions. In the four individual sessions the therapist ensure that the participant understand the schema model, manages crisis, and engages in schema therapy.

### Data analysis

Within-patient standardized effect size information (i.e., Cohen’s d) from baseline to end-of-treatment, and from baseline to follow-up will be calculated for eating psychopathology, and all secondary outcomes. Clinical outcome data will be analysed using intention to treat criteria. Data from outcome measures will be analysed with paired sample T-test. To assess group differences between the two treatment sites, independent t-tests will be used. The effect size of outcome measures will be compared to the effect size reported for previous studies CBT for eating disorders. The criterion used for statistical significance will be *p* < 0.05. Sample size was estimated assuming 80% power, significance level at 0.05, and an effect size of 0.5; 26 people are needed. Assuming a 50% drop out as documented in previous CBT trials, we will need around 40 people.

At the completion of the treatment, a random set of participants will be invited to provide qualitative feedback on their experiences of the group treatment. These interviews will be one-to-one, and conducted either face-to-face, or via telephone, and are expected to last for between 30 and 60 min. Transcripts of these interviews will be made and the data will be analysed using a thematic analyses approach. This information will be used to provide preliminary information about treatment efficacy and acceptability, and inform the design of future studies.

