### Measures

This study utilises a battery of assessments conducted at baseline, mid-treatment, end-of-treatment, and six- and twelve-month follow-up points. These assessments are conducted by fully registered psychologists who have received specialized training in the administration of standardized eating disorder measures. Table 1. Provides a summary of these assessments.

**Table 1 Tab1:** Assessments conducted at different time points

Measure	Baseline	Weekly	Mid	Post	6 months	12 months
EDE	x			x		
EDE-Q	x	x (abbrev)	x	x	x	x
YSQ-SF	x		x	x	x	x
SMI	x		x	x	x	x
WHO-5	x		x	x	x	x
CORE-10	x		x	x	x	x
SCS-SF	x		x	x	x	x
SATAQ	x		x	x	x	x
MCMI-III	x			x		
BSL-23	x			x	x	x

*Notes: EDE = Eating Disorder Examination; EDE-Q = Eating Disorder Examination- Questionnaire; YSQ-SF = Young Schema Questionnaire, short form; SMI = Schema Mode Inventory; WHO-5 = World Health Organisation-Five Well-Being Index; CORE-10 = Clinical Outcomes in Routine Evaluation-Outcome Measure; SCS = Self-Compassion Scale*- *Short Form; SATAQ = Sociocultural Attitudes Towards Appearance Questionnaire; MCMI-III = Millon Clinical Multiaxial Inventory- III; BSL-23 = Borderline Symptoms List*

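### As specified, the paired t-tests turn the promised intention-to-treat analysis into what is in effect a completer analysis, which may overstate the change

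*Protocol article*

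**What the plan says.** All of the relevant text is in the protocol article.

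- **Analysis population and test** (Data analysis, two adjacent sentences): "Clinical outcome data will be analysed using intention to treat criteria. Data from outcome measures will be analysed with paired sample T-test".
- **Effect measure** (same section): within-patient Cohen's d, "from baseline to end-of-treatment, and from baseline to follow-up will be calculated for eating psychopathology, and all secondary outcomes". These effect sizes are then to be compared with those of published CBT studies.
- **Sample size** (same section): "Sample size was estimated assuming 80% power, significance level at 0.05, and an effect size of 0.5; 26 people are needed", followed by "Assuming a 50% drop out as documented in previous CBT trials, we will need around 40 people".
- **Schedule** (Measures): a "battery of assessments conducted at baseline, mid-treatment, end-of-treatment, and six- and twelve-month follow-up points". Table 1 gives the EDE-Q at all five of these points, plus an abbreviated weekly form. Five other questionnaires and the SMI's schedule follow the same five points. The BSL-23 has no mid-treatment score. The EDE interview and the MCMI-III are taken only at baseline and post.
- **Primary outcome** (Primary outcomes): symptom severity on the EDE and the EDE-Q, with the EDE limited to pre and post.

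The article names no imputation and no model that tolerates missing scores. It does not say whether people who leave treatment are still assessed.

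**The concern.** Intention to treat means that everyone enrolled counts in the result. A paired t-test on observed scores counts only those who supplied both. With no missing scores the two agree, but this plan expects to lose half the sample.

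The sample-size text shows which reading the study was built on. If every enrolled participant contributed a pair, raising 26 to about 40 for drop-out would serve no purpose.

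The design makes this matter more. There is no control arm in which similar losses might partly offset the bias, so selective leaving passes straight into the within-group change. That change and its d are what will be set beside CBT results and, under Discussion, used to judge whether the therapy holds promise. Each later time point would also be tested on whichever subset happened to respond. The two-point tests ignore the mid-treatment scores, which are the best information on people who leave in the second half of treatment.

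**Working it through.** **1. Inputs.** From Data analysis: d = 0.5, alpha 0.05 (sidedness not stated), power 80%, 26 needed, drop-out 50%, about 40 enrolled. From Background: 6 of 8 completed in the earlier case series, and a cited review gives 29 to 73% drop-out in outpatient settings.

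**2. The plan's own figure.** Paired formula: n = ((z_alpha + z_power)/d)².
- One-sided 0.05: ((1.645 + 0.842)/0.5)² = 24.7, so 25; the exact t version gives 27. The stated 26 lies between them.
- Two-sided 0.05: ((1.960 + 0.842)/0.5)² = 31.4, so 32; the t version gives 34. The stated 26 does not reproduce.

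The 26 is therefore a count of complete pairs for a paired test, on a one-sided reading.

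**3. From 26 to 40.** Allowing for 50% loss gives 26/(1 − 0.5) = 52. The stated figure matches 26 × (1 + 0.5) = 39. That arithmetic is a separate matter. What counts here is that the step treats people who drop out as contributing no pair.

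**4. Pairs left.** 40 × (1 − 0.5) = 20. Power of the paired t-test at d = 0.5 with 20 pairs is 69.5% one-sided or 56.5% two-sided. With all 40 assessed it is 92.8% or 86.9%.

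**5. Completers against everyone enrolled.** Change over all = (1 − f) × completer change + f × leaver change. With completer change 0.50 SD, and leaver change assumed:

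| Drop-out f | Leavers change 0 | Leavers change 0.25 | Leavers change 0.50 |
|---|---|---|---|
| 50% | 0.25 | 0.375 | 0.50 |
| 25% (as in the case series) | 0.375 | 0.438 | 0.50 |

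**6. Simulation of 40 people with 50% drop-out.** The true mean change is 0.25 in SD units of change; rho is an assumed correlation between improving and staying.

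| rho | Mean change in completers |
|---|---|
| −0.3 | 0.02 |
| 0 | 0.25 |
| 0.3 | 0.49 |
| 0.5 | 0.64 |

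With no true change and rho = 0.3, the completer test declares improvement in 18% of trials, against a nominal 2.5% in that tail.

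**7. Would a repeated-measures model help?** Large-sample simulation; true change 0.50 SD; assumed correlations of 0.70 (baseline-mid), 0.60 (baseline-post) and 0.75 (mid-post); 50% drop-out; log-odds of leaving 0.5 to 2.0 per SD of poorer change.

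| Leaving depends on | Completer estimate | Model estimate |
|---|---|---|
| mid-treatment change, mid score observed | 0.64 to 0.85 | 0.50 |
| mid-treatment change, but mid score not collected | 0.64 to 0.85 | 0.60 to 0.77 |
| post-treatment change itself | 0.71 to 1.04 | 0.62 to 0.85 |

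The exact recovery in the first row is built in, because leaving there depends only on observed scores. With reversed slopes of −0.5 and −1.0 on mid-treatment change, completers give 0.36 and 0.26, which is too small.

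**The case against.** Intention to treat says who is analysed, and the t-test says how. The two fit together if leavers are still assessed, or if missing scores are imputed and the paired differences are tested afterwards. An article may leave that detail to an analysis plan that is not shown. Drop-out is not defined as loss to assessment: Background speaks of leaving treatment, and the schedule is not restricted to completers.

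This stands in part. A reader might infer that a paired t-test can never deliver intention to treat; that does not follow. The conflict is still in the stated text, however. The test is named, and the sample-size step counts drop-outs as lost to it.

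A reader might also infer that the result will overstate change. The documents do not support that. Nothing says that non-improvers leave more often, or when people leave. Steps 6 and 7 give no bias when leaving is unrelated to change, and a reversed bias when improvers leave.

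Three further objections stand. The 50% is a planning figure, and the earlier case series lost 2 of 8. The study is openly uncontrolled proof-of-concept work. A mixed model alone does not reach the EDE interview, which is one of the two primary instruments.

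**Conclusion.** The point holds in limited form. As specified, the main analysis is in effect a completer analysis labelled intention to treat, resting on about 20 of 40 pairs if the plan's own 50% drop-out occurs. It may overstate the change and d if people who improve less are likelier to leave.

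The one firm figure is the number of pairs, which follows from the plan's own assumptions. The halving from 0.50 to 0.25 SD assumes that leavers do not change at all. The simulated biases rest on assumed correlations and drop-out patterns, and show only that the effect could be large enough to alter the comparison with CBT. A statement that leavers are fully assessed, or that missing scores are suitably imputed, would remove the conflict; the article contains neither.

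**What to change.** 1. **Questionnaires measured at more than two points (EDE-Q and the others).** Replace the paired t-test with a mixed model for repeated measures. Include every enrolled participant with a baseline score, treat time as categorical, and use all scheduled full assessments, including mid-treatment where taken (the BSL-23 has none). Report baseline-to-post and baseline-to-follow-up change, and d as model-based change over baseline SD with a 95% CI.
2. **EDE interview and MCMI-III (baseline and post only).** Use multiple imputation informed by baseline and mid-treatment EDE-Q and other questionnaire scores.
3. **Sensitivity analyses.** Report the completer paired t-test and a not-missing-at-random analysis, for example baseline carried forward. The latter shrinks the estimate but does not protect the test: with no true change and rho = 0.3 it still declared improvement in 17.7% of simulated trials.
4. **Data collection.** In the groups still running, send the already scheduled self-report questionnaires to people who stop attending.

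**Cost.** Some analyst time and modest follow-up effort. The EDE is an interview, so post or email cannot supply it for leavers. Discussion reports four groups as having completed treatment, so post-treatment scores missed there are probably beyond recovery. The model relies on a missing-at-random assumption and helps little for people who leave before the mid-treatment assessment. The reported effect will probably be smaller.

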## Background

The treatment of eating disorders is a difficult endeavor, with only a relatively small proportion of clients responding to standard cognitive behavioural therapy (CBT). Less than half of those with bulimia nervosa (BN) have recovered at follow-up after receiving CBT [17, 18, 23] and research supporting cognitive-behavioural treatment for anorexia nervosa (AN) is limited, with no clear indication of improvement in this population [6, 8]. Approximately 50% of patients with eating disorders continue to be highly symptomatic at 60-week follow-up following transdiagnostic CBT [16]. Further, treatment dropout rates are high amongst individuals with eating disorders [9, 43] with one literature review reporting an average drop-out rate of between 20 and 51% in inpatient settings and between 29 and 73% in outpatient settings [20].

The treatment of eating disorders is especially complicated by a high level of co-morbidity [3]. Approximately 69% of individuals with eating disorders may meet DSM IV (APA, 1994) diagnostic criteria for a personality disorder and 93% of these clients may also have other co-morbidity including anxiety and substance use disorders. Eating disorders are also associated with the presence of rigid personality features, which increases clinical complexity and is associated with poorer treatment outcomes [22, 26, 46]. Eating disorders have also been linked to a range of trauma-related risk factors, including childhood abuse and neglect, which may also be mediated by personality disorder diagnoses [5]. Individuals with eating disorders also commonly experience complex and difficult-to-treat symptomatology including dissociation, perfectionism, compulsive pathology, rigid thinking patterns [28, 30, 38, 49] and high levels of shame [7].

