## Method

### Participants

Approximately 40 participants will be recruited into the study. All participants will be females aged 18 years and over, meeting *Diagnostic and Statistical Manual of Mental Disorders, 5th Edition* criteria for an eating disorder, following a transdiagnostic approach (Fairburn, et al., 2003). Participants are recruited via word of mouth, letters to clinicians and advertisements through *Facebook* as well as support organisations such as *The Butterfly Foundation.* Participants are provided with information about the study and, if they agree to participate, are required to give written consent. Full disclosure of the purpose of the study, the potential benefits and risks associated with participation, and the confidential nature of information obtained in the study is explained to participants.

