### Overall study design

This study will be an uncontrolled single group repeated measures design. Ethics approval was secured and participants provided informed consent to participate. Participants are first screened over the phone to ensure suitability for the group. If they agree to participate in the group, they then undergo a two-hour assessment where they complete a number of standard questionnaires and their diagnostic status is ascertained. Participants then commence treatment which consists of 25 weekly group sessions lasting for 1.5 h. Participants are also provided with four individual sessions that they can book with one of the therapists whenever they want. Each group consists of six to eight participants and is facilitated by two therapists, at least one of whom is a registered psychologist with training on schema therapy, and supervised by a schema therapist. Participants complete psychological measures and questionnaires at pre, post, 6 month and 1 year follow-up.

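### The drop-out allowance is miscalculated: keeping 26 participants after 50% loss needs 52 enrolled, not about 40, and the 20 pairs left give less than the stated 80% power whether the test is one- or two-sided

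*Protocol article*

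**What the plan says.** The sample size rationale stands in the Data analysis section of the protocol article. It opens with "Sample size was estimated assuming 80% power" and continues with "significance level at 0.05, and an effect size of 0.5; 26 people are needed". The next sentence makes the allowance for loss: "Assuming a 50% drop out as documented in previous CBT trials, we will need around 40 people". The Participants section carries the result forward as the recruitment target: "Approximately 40 participants will be recruited into the study". The Abstract and the Background also give n = 40.

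The design is a single group measured repeatedly ("This study will be an uncontrolled single group repeated measures design"), and the test is named: "Data from outcome measures will be analysed with paired sample T-test". The Data analysis section sets the significance criterion at p < 0.05 but does not say whether the test is one- or two-sided. It also refers to intention to treat, without saying how a missing post-treatment value would be handled. The Background reports drop-out from eating-disorder treatment of "between 29 and 73% in outpatient settings".

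**The concern.** Three figures in two consecutive sentences (26 needed, 50% lost, about 40 enrolled) cannot all be right. If half of 40 are lost, 20 remain, six short of the number the plan has just said it needs. The words around and approximately do not cover the gap, because 52 is 30% above 40.

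This calculation is the only justification given for the sample size. The Discussion makes the promise of the treatment depend on a reduction in symptoms being shown. A non-significant paired comparison would be read as coming from a study with 80% power, and the plan's own drop-out assumption does not support that.

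**Working it through.** **Inputs.** From the Data analysis section: paired t-test, alpha 0.05, power 80%, effect size 0.5, 26 analysable, 50% drop-out, about 40 enrolled. From the Background: outpatient drop-out of 29% to 73%. Two inputs are not given. Sidedness is not stated, so both cases are run. The scale of the 0.5 is not stated either, so it is taken as d, the mean paired difference divided by the SD of the paired differences.

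**Formula.** With n pairs the test statistic has n - 1 degrees of freedom and noncentrality d x sqrt(n). Power is the probability that this noncentral t exceeds the critical value for alpha 0.05, one- or two-sided.

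**Step 1: reproduce the 26.**

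- One-sided: the normal approximation gives ((1.645 + 0.842)/0.5)^2 = 24.7, so 25. The t-based answer is 27. At n = 26, power is 79.8%. The plan's 26 is reproduced to within rounding.
- Two-sided: the normal approximation gives ((1.960 + 0.842)/0.5)^2 = 31.4, so 32. The t-based answer is 34 (80.8% power). At n = 26, power is 68.8%. The plan's 26 is not reproduced.

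**Step 2: reproduce the 40.**

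- Correct inflation: n/(1 - drop-out) = 26/(1 - 0.5) = 52.
- Common slip: n x (1 + drop-out) = 26 x 1.5 = 39, which matches the stated figure.
- Drop-out at which 40 enrolled still yields 26: 1 - 26/40 = 35%.

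**Step 3: what 40 enrolled delivers at 50% drop-out.** 40 x 0.5 = 20 pairs.

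| Pairs | Power at d = 0.5, one-sided | Power at d = 0.5, two-sided | d with 80% power, one-sided | d with 80% power, two-sided |
|---|---|---|---|---|
| 26 | 79.8% | 68.8% | 0.50 | 0.57 |
| 20 | 69.5% | 56.5% | 0.58 | 0.66 |

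The inflation slip therefore costs about 10 percentage points one-sided (79.8 - 69.5) or about 12 two-sided (68.8 - 56.5). The detectable effect rises by 0.08 or 0.09.

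**Step 4: the drop-out range cited in the Background, with 40 enrolled.**

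- 29%: 40 x 0.71 = 28 pairs; power 82.5% one-sided, 72.3% two-sided.
- 73%: 40 x 0.27 = 11 pairs; power 46.0% one-sided, 32.3% two-sided.
- No loss: 40 pairs; power 92.8% one-sided, 86.9% two-sided.

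**Step 5: the drop-out that 40 enrolled can bear at 80% power for d = 0.5.**

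- One-sided: 27 pairs, so 1 - 27/40 = 32.5%.
- Two-sided: 34 pairs, so 1 - 34/40 = 15%.

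At 50% drop-out a two-sided test would need 34/0.5 = 68 enrolled, so even 52 would not be enough on that basis.

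**The case against.** The strongest reply is that drop-outs need not be lost to the analysis. The plan invokes intention to treat, and the 50% comes from earlier CBT trials, where it may mean leaving treatment rather than failing to return questionnaires. If nearly all 40 supply post-treatment data, two-sided power is about 87%. This stands as a condition and belongs in the text. It does not rescue the sentence as written: the plan's own inflation step treats drop-outs as lost, since otherwise no inflation would be needed. A paired t-test needs both measurements, and the article gives no rule for supplying a missing one.

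A second reply is that this is an uncontrolled proof-of-concept study whose results will also be reported as within-patient effect sizes, and that enrolment is largely settled: the Discussion reports four groups completed and two begun, of the six planned. That limits the consequence and argues against asking for more participants. It does not make the arithmetic right.

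A reader might go further and infer that the drop-out slip alone takes power from 80% to 56%, or the detectable effect from 0.50 to 0.66. The documents do not support that. The 80% at 26 pairs and the 0.50 hold only one-sided, while the 56% and the 0.66 are two-sided. On a two-sided reading, about 11 of the points below 80% are already missing at 26 pairs, before any drop-out.

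**Conclusion.** The enrolment figure is wrong as printed. On the plan's own inputs 52 are needed rather than about 40, and 40 leaves 20 pairs. This part needs no assumption beyond the stated 26 and 50%.

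The resulting power is about 70% if the test is one-sided, the basis on which the 26 reproduces, and about 56% if it is two-sided, where 26 pairs would give only about 69%. On neither basis does 40 enrolled with 50% drop-out give 80%.

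The power figures rest on two assumptions: that the 0.5 is standardised by the SD of the paired differences, and that drop-outs supply no post-treatment value. If the 0.5 were instead standardised by a common SD at each time point, the answer would depend on the pre-post correlation r through d = 0.5/sqrt(2(1 - r)). The t-based requirement for 80% power would then be 46 pairs two-sided (37 one-sided) at r = 0.3 and 21 (17) at r = 0.7. The article gives no correlation. The inflation error is the same in every case.

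**What to change.** State the sidedness of the test and replace the drop-out sentence. No extra enrolment is asked for; six groups of at most eight hold 48, so 52 is out of reach of the planned groups in any case. Possible wording:

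> With 40 enrolled and 50% drop-out, 20 complete pairs are expected, giving about 56% power two-sided (70% one-sided) for d = 0.5, and 80% power for d = 0.66 two-sided (0.58 one-sided). For d = 0.5, 80% power needs 34 pairs two-sided (about 27 one-sided), that is, drop-out of no more than about 15% (about 33% one-sided). If post-treatment data are obtained from nearly all 40 regardless of attendance, power is about 87% two-sided.

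Once the sidedness is fixed, keep only the figures for that case. If the test is two-sided, 26 should not stay in the text as an adequate number of pairs. Add a few words on what the 0.5 is standardised by.

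The cost is a few sentences and a less favourable power statement. Design, recruitment and treatment are unchanged.

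### The stated 80% power is not shown to be the power of the intention-to-treat analysis at 40, because the plan does not say whose effect the 0.5 is

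*Protocol article*

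**What the plan says.** All of this stands in one paragraph of the protocol article, under Data analysis.

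- Analysis set: "Clinical outcome data will be analysed using intention to treat criteria".
- Test: "Data from outcome measures will be analysed with paired sample T-test". The significance criterion is p < 0.05, with no statement of one or two sides.
- Size: "Sample size was estimated assuming 80% power, significance level at 0.05, and an effect size of 0.5; 26 people are needed".
- Allowance for drop-out: "Assuming a 50% drop out as documented in previous CBT trials, we will need around 40 people".

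The paragraph does not say whether 0.5 is meant for everyone enrolled or for those who complete. It also does not say whether drop-out means leaving treatment, losing the outcome measurement, or both.

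**The concern.** A power figure belongs to a particular analysis in a particular set of people. Raising 26 to allow for drop-out is the usual step when drop-outs contribute no data and the assumed effect holds in those who are left. Intention to treat, as commonly understood, counts everyone enrolled. The two can be reconciled, but only by saying whose effect the 0.5 is and what drop-out removes, and the paragraph says neither.

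With half the sample assumed to drop out, the choice matters a great deal. The study is meant as proof of concept, and its effect sizes are to be set beside those of earlier CBT studies. A non-significant intention-to-treat result in a study believed to have 80% power could be taken as evidence that the therapy does not work, when the power of that analysis may have been much lower.

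**Working it through.** **Inputs from the Data analysis section:** significance level 0.05, power 80%, effect 0.5 (taken as mean within-patient change divided by the SD of change), paired t-test, 50% drop-out, about 40 enrolled. Sidedness is not stated, so both are shown. **Assumption not in the document:** the gain in drop-outs, varied below.

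**Step 1. The plan's 26.** The normal approximation is n = ((z_alpha + z_power) / d)².
- One-sided: ((1.645 + 0.842) / 0.5)² = 24.7, so 25. The noncentral t gives 27, and power at 26 is 79.8%.
- Two-sided: ((1.960 + 0.842) / 0.5)² = 31.4, so 32. The noncentral t gives 34, and power at 26 is 69%.

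So 26 reproduces only as a one-sided figure.

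**Step 2. The plan's 40.** With half lost, 26 / (1 − 0.5) = 52, while 26 × 1.5 = 39 is close to 40. Enrolling 40 and losing half leaves 40 × 0.5 = 20 pairs.

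**Step 3. Effect over all enrolled if 0.5 is the completers' effect.** Let half have mean change 0.5 and SD 1, and the other half have mean change m.
- Drop-outs with SD 1: d = (0.25 + 0.5m) / √(1 + 0.25(0.5 − m)²).
  - m = 0: 0.25 / √1.0625 = 0.243
  - m = 0.25: 0.375 / √1.0156 = 0.372
  - m = 0.5: 0.5
- Drop-outs carried at exactly zero change: SD = √(0.5 + 0.0625) = 0.75, so d = 0.25 / 0.75 = 0.333.

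**Step 4. Power at 40 enrolled** (noncentral t with n − 1 degrees of freedom and noncentrality d√n; where two figures are given, the second is by simulation).

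| Case | n analysed | d | Two-sided | One-sided |
|---|---|---|---|---|
| Drop-outs' outcomes lost, 0.5 holds in the rest | 20 | 0.5 | 56% | 70% |
| All analysed, drop-outs gain nothing, same SD | 40 | 0.24 | 32% | 45% |
| All analysed, drop-outs carried at zero change | 40 | 0.33 | 54–56% | 67–70% |
| All analysed, drop-outs gain half | 40 | 0.37 | 63% | 75% |
| All analysed, drop-outs gain the same (0.5 is then also the effect in all enrolled) | 40 | 0.5 | 87% | 93% |

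**Step 5. Where 80% is met.** With all 40 analysed, 80% power needs d of about 0.454 two-sided or 0.400 one-sided. Ignoring the small rise in SD, d = 0.25 + 0.25f, where f is the share of the completers' gain that drop-outs keep. This gives f of about 82% two-sided or 60% one-sided.

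**Step 6. Would 52 settle it?** Not by itself. At 52 enrolled and all analysed, two-sided power is 40% (no gain, same SD), about 66% (carried at zero change) and 75% (half the gain).

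**The case against.** The best reply is that there need be no conflict. If 0.5 is the effect in all enrolled and drop-out means that post-treatment scores are lost, then enrolling more people to make up for lost information is sound practice alongside intention to treat. This is correct, and it rules out a stronger reading that a reader might infer: that the sample-size calculation and the analysis must refer to different populations whatever 0.5 means.

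A second tempting inference is that intention to treat keeps the drop-outs in, dilutes 0.5, and leaves the study underpowered. The document does not support this as a fact. It never calls 0.5 a completers' effect and gives no effect for drop-outs. Whether they are measured, imputed, carried forward or left out is a matter commonly settled in an analysis plan, and its absence here is no fault. The 0.5 may already be cautious: the Background reports d = 1.70 for eating disorder severity in a case series of eight. For illustration, if completers changed by 1.70 SD and half the sample gained nothing with the same SD, d would be 0.85 / √(1 + 0.25 × 1.70²) = 0.65, and two-sided power at 40 about 98%.

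Third, setting two-sided powers against an 80% that 26 reproduces only one-sided would mix two issues. That is right, and it is why both columns are given.

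What remains is narrower. Even on the reading most favourable to the plan's logic, where outcomes are lost and 0.5 applies to everyone, 40 enrolled leaves 20 pairs and 56% or 70% power. If nobody's data are lost and 0.5 applies to everyone, power is 87% or 93%. None of the cases tabulated gives 80%.

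**Conclusion.** The point holds in a limited form. The paragraph attaches 80% power to a planned size of about 40 and to an intention-to-treat analysis without showing that this analysis has that power, and without saying to whom the 0.5 applies. At 40 enrolled with 50% drop-out, power in the cases computed runs from 32% to 87% two-sided and from 45% to 93% one-sided. With all 40 analysed and 0.5 as the completers' effect, 80% is reached only if drop-outs keep about 82% (two-sided) or 60% (one-sided) of the completers' gain.

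These figures rest on a paired effect of 0.5 and on assumed gains in drop-outs that the document does not supply. The direction of the error is therefore conditional: power may be well below 80% or somewhat above it. It would be wrong to conclude that the study is shown to be underpowered or that the plan contradicts itself outright. The stated figure is unsupported for the stated analysis, and it should be restated.

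**What to change.** In the Data analysis section:

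1. State that the assumed effect applies to all enrolled participants under intention to treat.
2. Name the sidedness of the test, since 26 reproduces only one-sided.
3. Replace the unqualified 80% with the power at 40 across the cases in the table: outcomes lost with 20 pairs left, and all 40 analysed with drop-outs gaining nothing, half or the same. Where 0.5 is reached only by completers, give the resulting all-enrolled effect (0.24, 0.33 or 0.37) beside each power, and label the drop-outs' gain as an assumption.

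This takes about two sentences and a short list of figures. It needs no extra participants, which matters because the Discussion reports four groups completed and two more begun, out of the six planned. The cost is a stated power that is less favourable in most of the cases.
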